## 10. Limitations 

The blinding of participants is not feasible for this trial due to the nature of the intervention. While the non-blinded design may introduce bias in outcome assessment [41], care has been taken to mitigate bias through cluster randomization and ensuring that outcome assessors are assigned to only one study group over the intervention period. 

The 90-day intervention period may not capture long-term effects on wound healing, potentially missing essential insights into the sustainability and long-term impact of the intervention. Hence, outcome measurements at 6 months and 1 year and an economic evaluation alongside the cluster RCT have been planned to determine if this intervention period is adequate.

The focus on community settings in Singapore may also affect the generalizability of the results to other healthcare systems. However, as pressure injury management requires an extended period of care and is generally not managed within a fixed healthcare setting and environment, the findings will contribute to evidence-based management, improving patient outcomes and healthcare cost-effectiveness. The study’s potential impact on policy and practice, considering the unique healthcare financing and reimbursement landscape in Singapore for nutritional intervention [14], adds to its relevance and importance.

## 11. Conclusions

This trial is designed to provide insights into the effectiveness of a comprehensive PI nutrition and nursing care bundle intervention. The focus on both clinical and economic aspects sets this study apart from previous interventions. The integration of education, intensive dietetic support, and nutrition-trained home care/community nurses in nutrition care offers a holistic approach to PI management.

## Figures and Tables

**Table 1 nutrients-16-00299-t001:** Exclusion criteria for the INCA Trial.

	Exclusion Criteria
1.	Septicaemia.
2.	Poorly controlled diabetes (*glycated hemoglobin level > 8.5%)* [20,26].
3.	Consumption of supplements will lead to fluid intake in excess of fluid restriction for the following conditions: Advanced renal disease not on dialysis (KDIGO [21,22] Stage G4 with an eGFR of 15–29 mL/min/1.73 m^2^ and Stage G5 with an eGFR of less than 15 mL/min/1.73 m^2^); Heart failure with reduced ejection fraction [27]; Advanced decompensated alcoholic and non-alcoholic liver cirrhosis [28,29].
4.	Current neoplastic disease or last chemotherapy or radiotherapy less than one year ago.
5.	Currently on immunosuppressive therapy.
6.	Palliative with *a lifespan of ≤ 3 months.*
7.	Known allergy reaction to L-arginine or phenylketonuria.
8.	Presence of an infected wound *(if it is the only pressure injury present on the participant).*
9.	Untreated diagnosed osteomyelitis [18,19,30,31,32].
10.	Pregnant women and children (there is limited evidence on the use of arginine in these groups).

**Table 2 nutrients-16-00299-t002:** Outcomes and the methods of measurement to be used in the cluster RCT.

Type	Outcome	Outcome Description	Measurement Method	Data Collection Time Point (t) and Time Frame	Performed by
Primary	Wound	Change in the area of pressure injury (cm^2^) from the baseline	Assessed by the change in wound area ^#^ from the baseline to the follow-up time points and measured with a 3D wound imaging device at the time of follow-up.	t_0_ baseline, t_1_ 30 days, t_1_ 60 days, t_3_ 90 days, t_4_ 6 months, and t_x_ 1 year Time frame: 1 year	Nurse
		The proportion of participants with ≥40% area reduction	Assessed by the number of participants with wound area ^#^ reduction ≥ 40% at the time of follow-up versus the baseline.	t_1_ 30 days, t_1_ 60 days, t_3_ 90 days, t_4_ 6 months, and t_x_ 1 year Time frame: 1 year	Nurse, CRC
Secondary	Wound	The proportion of participants with complete wound healing of the main wound	Assessed by the number of participants with complete healing of a wound ^#^, determined by clinical assessment and pressure injury staging.	t_1_ 30 days, t_1_ 60 days, t_3_ 90, t_4_ 6 months days, and t_x_ 1 year Time frame: 1 year	Nurse, CRC
		The proportion of participants with increased severity of pressure injury (PI stage)	Assessed by the number of participants with increased severity of wound ^#^ at follow-up. The severity of pressure injury is determined by the increase in pressure injury staging or the increase in the area of the wound if pressure injury staging remains the same at the follow-up time points.	t_1_ 30 days, t_1_ 60 days, t_3_ 90, t_4_ 6 months, and t_x_ 1 year Time frame: 1 year	Nurse, CRC
		The proportion of participants with a new wound infection	Assessed of the number of participants with new wound infection(s) at follow-up who are clinically diagnosed with confirmation from blood tests (e.g., C-Reactive Protein CRP, renal, and liver function tests).	t_1_ 30 days, t_1_ 60 days, t_3_ 90 days, t_4_ 6 months, and t_x_ 1 year Time frame: 90 days	Nurse
	Nutritional	Change in nutritional status	Assessed using the Global Leadership Initiative on Malnutrition (GLIM) criteria to determine the severity of malnutrition. Change in the nutritional status determined by the direction of the nutritional status shift from the baseline to follow-up.	t_1_ 30 days, t_1_ 60 days, t_3_ 90 days, and t_x_ 1 year Time frame: 1 year	Nurse, Dietitian
		Change in nutritional intake	Assessed by the change in average of energy, protein, and selected micronutrient intake derived from 3DFR. Three-day food records will be filled by the participants or caregivers at selected time points. If the family or participant is unable to fill out the record, photographs of meals can be taken by the subject or caregiver and sent to the CRC. Trained personnel will use food composition analysis software (DietPlan 7, Forestfield Software Ltd., UK) to determine the intake, adjusted to per unit kilogram weight of the participant The energy, protein, and micronutrient intake of the study subjects on enteral tube feeding will be determined by a calculation of the goal feeding regimen that the study subject has been prescribed prior to the start of the study.	t_0_ baseline, t_1_ 30 days, and t_1_ 60 days Time frame: 60 days	Dietitian, Nurse
	Quality of Life	Change in HRQOL	Assessed by the change in EQ5D-5L VAS and utility scores at follow-up from the baseline for the overall population and age categories, if appropriate, where changes in scores are expressed as mean differences or standardized mean differences.	t_0_ baseline, t_3_ 90 days, t_4_ 6 months, and t_x_ 1 year Time frame: 1 year	Dietitian, Nurse, CRC
	Clinical	Mortality	Assessed by the occurrence and time-to-event of all-cause mortality during the study period.	t_1_ 30 days, t_1_ 60 days, t_3_ 90 days, and t_x_ 1 year Time frame: 1 year	Nurse, CRC
		Unplanned hospital admissions	Assessed by the occurrence and time-to-event of one or more unplanned hospital admissions during the study period.	t_1_ 30 days, t_1_ 60 days, t_3_ 90 days, and t_x_ 1 year Time frame: 1 year	Nurse, CRC
Others	Pre-specified Outcome	Adherence to nutrition Supplementation intake	Assessed by the number of participants with >75% consumption of oral nutritional supplements and Arginaid, where the servings of products consumed are counted with confirmation of intake during follow-up.	t_1_ 30 days, t_1_ 60 days, and t_3_ 90 days Time frame: 1 year	Dietitian, Nurse, CRC
		Wound depth	Measured (millimeters) using sterile forceps and rulers at follow-up.	t_0_ baseline, t_1_ 30 days, t_1_ 60 days, 90 t_3_ days, and t_x_ 1 year Time frame: 1 year	Nurse
		Hospital length of stay	Assessed by the number of days for each unplanned hospital admission.	If available: t_x_ 1 year Time frame: 1 year	Nurse, CRC
		Wound duration and time-to-heal	Measured by days to complete healing for participants with complete wound healing. Additional interaction of time with intervention and other covariates will be included and tested	t_x_ 1 year Time frame: 1 year	Investigators
		Frequency of unplanned hospital admissions	Assessed by the frequency of occurrence per participant and the sum of unplanned hospital admissions of all participants.	t_x_ 1 year	Investigators

^#^ The data from the measurement of the pressure injury with the highest severity will be used in the analysis for the primary endpoint. If the wound of the highest severity is deemed unmeasurable (e.g., too small of a surface area), we will select the wound with the next highest severity. CRC: clinical research coordinator; HRQOL: health-related quality of life; PI: pressure injury.

**Table 3 nutrients-16-00299-t003:** Study schedule of enrolment, interventions, and assessments.

	STUDY PERIOD							
	Enrollment	Allocation	Post-Allocation					Close-Out
TIMEPOINT	*−7 to −1d* −*t_0_*	Baseline *t_0_*	*30d t_1_*	*60d t_2_*	*90d t_3_*	*6m t_4_*		*1y* *t_x_*

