### 2.3. Inclusion and Exclusion Criteria 

Patients will be considered eligible if they are able to provide written informed consent (patient or legal guardian). The patients can be on oral and/or enteral nutritional support. The exclusion criteria for the trial are presented in Table 1.

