### 2.9. Intervention

Based on the latest guidelines, the intervention group will receive an educational pamphlet on nutritional and wound care for participants/families, with an in-depth explanation by trained nursing staff and a research dietitian. The trained nurses will reinforce nutritional education (adequate energy protein/fluid intake and compliance to consumption of supplements) on visits without a dietitian. The nutritional intervention provided will be based on the “The European Pressure Ulcer Advisory Panel, the National Pressure Injury Advisory Panel, and the Pan Pacific Pressure Injury Alliance Prevention and Treatment of Pressure Ulcers/Injuries: 2019 Clinical Practice Guideline” [1,33].

A dietetic consultation at the baseline, day 30, and day 60 of the intervention will be performed by an experienced and trained research dietitian on optimizing nutritional intake to meet caloric/protein requirements, along with additional high protein high energy (HPHE) supplementation (commercial ONS) prescribed for participants who do not meet nutritional requirements (25–35 kcal/kg/d and 1.2–2.0 g protein/kg/d) [1,33]. The dietetic consultation will be performed via face-to-face home visits and/or teleconsultation (depending on participant and caregiver preference). Adjustments to the enteral feeding regimen will be made for patients who did not see a dietitian during their last hospital admission. 

A specialized nutritional supplement for wound healing (Arginaid, Nestle, Vevey, Switzerland) containing 4.5 g arginine, 156 mg Vitamin C, 40.9 mg alpha-tocopherol equivalents (Vitamin E), and 30 kcal will be administered twice a day via oral ingestion or tube feeding (mixed in 100 mL water) for 12 weeks (14 servings per week). Adherence to supplementation will be determined by recording the number of leftover products by participants or their caregivers, with confirmation of intake during the research dietitian or nurse visit on days 30, 60, and 90. 

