## 8. Data Collection and Management

### 8.1. Data Collection 

Data will be collected by the nurses (for both groups) and the research dietitian (for the intervention group only) during each planned visit (Table 2). This will be carried out at the baseline, 30 days, 60 days, 90 days, and 12 months for the wound and nutritional data, hospital admissions, mortality, and health-related quality of life (HRQOL). The study schedule of enrolment, interventions, and assessments follows the recommendations from the SPIRIT statement [23] and the SPIRIT-OUTCOMES extension [24], as shown in Table 3.

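### Table 2 computes tube-fed participants' intake from their pre-study prescription, so their change in intake is zero by construction and any true arm difference among them is masked

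*Protocol article*

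**What the plan says.** All references are to the protocol article.

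- **Outcome.** The Nutritional rows of Table 2 include change in nutritional intake: "Assessed by the change in average of energy, protein, and selected micronutrient intake derived from 3DFR". The time points in that row are baseline, 30 days and 60 days.
- **Tube-fed rule.** The same cell says the intake of participants on enteral tube feeding is "determined by a calculation of the goal feeding regimen that the study subject has been prescribed prior to the start of the study". It gives no other rule for them.
- **Eligibility.** Section 2.3: "The patients can be on oral and/or enteral nutritional support". The expected tube-fed share is not given.
- **Intervention.** Section 2.9: "Adjustments to the enteral feeding regimen will be made for patients who did not see a dietitian during their last hospital admission". The supplement "will be administered twice a day via oral ingestion or tube feeding", and each serving contains 4.5 g arginine, "156 mg Vitamin C, 40.9 mg alpha-tocopherol equivalents (Vitamin E), and 30 kcal".
- **Who collects.** Section 8.1: "Data will be collected by the nurses (for both groups) and the research dietitian (for the intervention group only) during each planned visit". Section 2.7 likewise confines the research dietitians' contact to the intervention arm. Table 2 names nurse and dietitian for GLIM status and for intake, and dietitian, nurse and coordinator for EQ-5D.

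**The concern.** A change score needs a follow-up value that can differ from baseline. The tube-fed rule supplies a single number, set before the trial begins. It also records a goal rather than what was delivered. Whatever the intervention does to a tube-fed participant's feeding, the outcome cannot register it.

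The intake outcome is the one that shows whether the nutritional component changed nutrition. If part of the sample contributes zeros by definition, the estimated arm difference is pulled towards zero. A null wound result could then be misread as a failure to raise intake when the measurement could not have shown a rise.

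A separate and smaller matter is who does the measuring. The staff who deliver dietetic care may also record some secondary outcomes, and they do so in one arm only. That allows assessor type to differ by arm.

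**Working it through.** The plan states no figure for this point, so there is none to reproduce. The check compares sections and adds simple arithmetic.

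**Step 1: change under the rule.** Let P be the intake implied by the pre-study goal regimen. Under Table 2, baseline = P, day 30 = P and day 60 = P, so change = P − P = 0 in either arm. For someone fed both orally and by tube, this applies to the tube-fed part. Table 2 expresses food-record intake per kilogram. If that scaling is also applied to tube feeds with updated weights, the only movement would come from weight, not intake.

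**Step 2: what the rule omits.** For a fully adherent tube-fed intervention participant, two servings per day (section 2.9) supply:

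- energy 2 × 30 = 60 kcal
- arginine 2 × 4.5 = 9 g
- vitamin C 2 × 156 = 312 mg
- vitamin E 2 × 40.9 = 81.8 mg

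Any regimen adjustment is omitted as well. Table 2 does not say which micronutrients are selected, so the vitamin figures matter only if those vitamins are among them.

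**Step 3: dilution of the overall difference.** Let f be the tube-fed share, d the true arm difference in orally fed participants, and r × d the true arm difference in tube-fed participants.

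- True overall difference = (1 − f)d + f·r·d
- Measured overall difference = (1 − f)d
- Retained share = (1 − f) / [(1 − f) + f·r]

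Neither f nor r is in the document, so both are assumed here.

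| f (assumed) | Retained, r = 1 | Retained, r = 0.5 | Vitamin C omitted from intervention-arm mean (f × 312) |
|---|---|---|---|
| 0.2 | 0.80 | 0.80/0.90 = 0.89 | 62.4 mg/day |
| 0.3 | 0.70 | 0.70/0.85 = 0.82 | 93.6 mg/day |
| 0.5 | 0.50 | 0.50/0.75 = 0.67 | 156 mg/day |

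Among fully tube-fed participants the retained share is zero for any r above zero.

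**Step 4: where assessor type can differ by arm.** Dietetic consultations fall at baseline, day 30 and day 60. Section 2.9 also allows a dietitian or nurse visit at day 90.

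- *GLIM status* (follow-up at 30, 60 and 90 days and 1 year) coincides with dietitian visits at days 30 and 60, and possibly 90. This is the clearest exposure.
- *Oral intake* is recorded by participants or caregivers and analysed by trained personnel with software, so the exposure is weaker.
- *EQ-5D* (baseline, 90 days, 6 months, 1 year) overlaps at baseline and at most day 90. No dietitian contact is described at 6 months or 1 year.

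The size of any assessor effect cannot be computed from the document.

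**The case against.** Several counter-arguments have force.

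- **The rule may be meant for baseline only.** The sentence names no visit. But it is the only rule given for tube-fed participants, in a row that lists three time points. Read as baseline only, it leaves no follow-up rule, and the wording still needs correcting.
- **The enteral gain may be small.** Section 2.9 limits regimen adjustment to those not seen by a dietitian at their last admission, and section 1 says such patients are routinely reviewed by dietitians in acute care. This stands. Equal gain by route is therefore an assumption, and the loss is smaller if the enteral gain is smaller.
- **Supplement servings are counted elsewhere.** The adherence row of Table 2 counts them at days 30, 60 and 90, so the supplement part is recoverable. This stands too and makes the fix cheap, but the intake row does not use those counts, and they do not capture regimen changes.
- **Assessment is already unblinded and forms are standardised.** Sections 2.8 and 10 say so. Nurses are unblinded, each attends one arm only, and those in the intervention arm reinforce the intervention. A common assessor type therefore reduces the risk without removing it.

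Stronger readings are tempting, but the document does not support them. A reader might infer that observed arm differences in intake are artefacts; a fixed value hides a difference and cannot create one. A reader might infer that a planned oral-versus-enteral comparison of intake is spoiled; section 5.3 lists route as a subgroup but does not name intake as the outcome. A reader might infer that dietitian assessment tilts EQ-5D, and hence the QALYs in section 6.2, towards the intervention. The dietitian is one listed collector among three, the overlap is limited, and no direction of bias is shown.

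**Conclusion.** The tube-feeding rule defeats the outcome it serves. Read as the rule for every time point in its row, it makes tube-fed change in intake zero in both arms, contrary to section 2.9. Any true arm difference among tube-fed participants is masked. The overall difference is diluted to between 80% and 50% of its true value if 20% to 50% are tube-fed and gains are equal by route, or to between 89% and 67% if the enteral gain is half the oral gain. Those ranges rest on assumed shares and gains; the zero does not.

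The assessor point is a possible bias, not a demonstrated one. It is clearest for GLIM status and weaker for intake and for EQ-5D at baseline or day 90.

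Both matters concern secondary outcomes. Change in intake is secondary in Table 2 and does not appear in the section 3.2 list. Wound area is measured by nurses, so the primary outcomes are unaffected. The sponsor should correct this, but it does not threaten the main trial result.

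**What to change.** 1. Reconcile Table 2 with section 2.9. Use the pre-study prescription as the baseline value only. At each follow-up visit, compute tube-fed intake from the regimen in force at that visit (delivered volume where recorded), plus the trial supplement servings already counted for adherence. State how mixed oral and tube feeding is combined.
2. While editing that row, align its time points with Table 3, which marks the food record at baseline and day 60 but not at day 30.
3. Have the nurse or coordinator collect GLIM status, food records and EQ-5D in both arms on the same form. Keep dietitian records for intervention delivery and adherence. Acknowledge that unblinded, arm-specific nurses leave some risk in place.

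The cost is table and form wording, an entry for the current regimen at follow-up visits, and a small shift of work from dietitian to nurse or coordinator in the intervention arm. Nurses already collect data in both groups, so no new staff should be needed.

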### 3.2. Secondary Outcome Measurements

Proportion with Increased Severity in Pressure Injury Stages: The percentage of participants whose pressure injury progresses in severity (PI stage and area of wound);Proportion with Complete Pressure Injury Healing: The percentage of participants whose PIs fully heal;Proportion with Improvement in Health-Related Quality of Life (HRQOL): The percentage of participants showing enhancements in HRQOL, as measured by the standardized instrument EQ-5D-5L;Proportion with Nutritional Status Improvement: The percentage of participants with measured nutritional advancements;Change in HRQOL (EQ-5D-5L Utility Values and VAS): The measured alteration in HRQOL utilizing EQ-5D-5L utility values and Visual Analog Scale (VAS);Incidence of New PIs: The number of new PIs during the study period;Incidence of PI Wound Infections: The number of new infections in PI wounds during the study period;Mortality Rate: The death rate among participants during the study time frame;Unplanned Hospital Admissions and Length of Stay (LOS): The frequency and duration of unexpected hospital admissions within the participant group.

All the study data and outcome measurements listed in Table 2 will be recorded using the Research Electronic Data Capture (REDCap) system [34]. Sociodemographic data will be collected based on recommendations by a local systematic review of healthcare utilization in urban Singapore [35]. 

A window period of ±14 days will be implemented for all assessments and outcome measurements. If an outcome measurement is interrupted (e.g., malfunction of wound imaging equipment, secure cloud server downtime, or assessors unable to visit on the day of assessment due to participant’s request for postponement), the assessor will re-attempt the measurement within the window period. Any outcomes measured outside of this window period will be considered a protocol deviation. 

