### 5.1. Outcome Measures

Dichotomous Outcomes: The frequency of outcomes will be determined, and we will utilize time-to-event analyses. The hazard ratios (HRs) along with their 95% confidence intervals (CIs) will be determined using a stratified Cox proportional hazards model.Continuous Outcomes: The differences between the intervention and control groups, along with their 95% CIs and corresponding *p*-values, will be documented.

Both patient-level and cluster-level data will be analyzed. We will address any imbalances in individual data by adjusting statistically using a mixed-effects Cox regression model performed by a statistician blinded to the group allocation. 

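### Hospital length of stay is defined per admission, so never-admitted participants have no value and mean stay can rise while total hospital days fall

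*Protocol article*

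**What the plan says.** Three places in the protocol article bear on this outcome.

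- **Table 2, block headed Others, row on hospital length of stay.** The measurement method is "Assessed by the number of days for each unplanned hospital admission", with the time point given as "If available: t_x_ 1 year Time frame: 1 year".
- **Section 3.2.** Unplanned admissions and length of stay appear together in the list of secondary outcomes, described as "The frequency and duration of unexpected hospital admissions within the participant group". No unit is given.
- **Table 3.** Unplanned hospitalisation and length of stay are marked at 30, 60 and 90 days, 6 months and 1 year.

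Two neighbouring rows of Table 2 work at participant level. One is occurrence and time to first admission: "Assessed by the occurrence and time-to-event of one or more unplanned hospital admissions during the study period". The other is admission frequency: "Assessed by the frequency of occurrence per participant and the sum of unplanned hospital admissions of all participants".

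On analysis, section 5 commits to intention to treat with all randomised subjects analysed. Section 5.1 says of continuous outcomes: "The differences between the intervention and control groups, along with their 95% CIs and corresponding *p*-values, will be documented". It adds: "Both patient-level and cluster-level data will be analyzed". No model is named for continuous outcomes, and no admission-level analysis is mentioned.

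**The concern.** Postal codes are randomised and participants are followed, but this outcome has the admission as its unit. Being admitted happens after randomisation, and the trial lists it as an outcome in its own right. If the bundle changes who is admitted, the admitted participants in the two arms are no longer comparable groups. A difference in days per admission then mixes two things: the effect on how long stays last, and the effect on which stays occur at all.

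What is at stake is interpretation. A reader of the trial report wants to know whether the bundle reduces time in hospital. Mean days per admission does not answer that and can move in the opposite direction.

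**Working it through.** **No stated figure to reproduce.** The article gives no admission rate, mean stay or power for this outcome. The only planning number used below is the 190 participants per arm from section 2.4. Everything else is an assumption.

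**Step 1. Who has a value.** With days per admission, a participant with zero admissions contributes nothing. The share without a value depends on the admission rate:

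| Assumed admissions per person | Share never admitted | Of 190 per arm |
|---|---|---|
| Mean 0.6, Poisson | exp(−0.6) = 0.55 | about 104 |
| Mean 0.8, negative binomial, k = 1 | 1/(1 + 0.8) = 0.56 | about 106 |
| Mean 1.5, negative binomial, k = 1 | 1/(1 + 1.5) = 0.40 | 76 |
| Mean 1.5, negative binomial, k = 0.5 | (1 + 1.5/0.5)^(−0.5) = 0.50 | 95 |

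Under these assumptions, 40% to 56% of randomised participants drop out of the comparison. A model for repeat stays does not change this, because it still has no observation for people never admitted.

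**Step 2. Direction.** Two hypothetical examples, 190 per arm.

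*Example A.* Control has 100 stays of 5 days and 60 of 20 days. The intervention arm has 50 and 60.
- Total days: 100×5 + 60×20 = 1,700, against 50×5 + 60×20 = 1,450. Ratio 0.853, a fall of 15%.
- Mean per admission: 1,700/160 = 10.6, against 1,450/110 = 13.2. Ratio 1.24, a rise of 24%.
- Days per randomised participant: 1,700/190 = 8.95, against 1,450/190 = 7.63.

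*Example B.* Control has 100 stays of 4 days and 60 of 14 days. The intervention arm has 50 and 55.
- Total days: 1,240 against 970, a fall of 22%.
- Mean per admission: 1,240/160 = 7.75, against 970/105 = 9.24, a rise of 19%.
- Days per randomised participant: 6.53 against 5.11.

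The reversal needs only that the prevented admissions are mostly short ones.

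**Step 3. Repeat stays, only if they were tested as independent.** The article does not say this. For scale, the type I error of such a test is 2×(1 − Φ(1.96/√DE)), where DE = 1 + (m_eff − 1)×ρ and m_eff = E[m²]/E[m]. Here m is the number of admissions per admitted participant and ρ the within-person correlation of stay.

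| Admitted participants with 1, 2, 3… stays | m_eff | ρ = 0 | ρ = 0.1 | ρ = 0.3 | ρ = 0.5 |
|---|---|---|---|---|---|
| 80/15/5% | 1.85/1.25 = 1.48 | 5.0% | 5.6% | 6.7% | 7.8% |
| 60/25/10/5% | 3.30/1.60 = 2.06 | 5.0% | 6.2% | 8.8% | 11.3% |
| 40/30/15/10/5% | 5.80/2.10 = 2.76 | 5.0% | 7.1% | 11.3% | 15.3% |

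A simulation (380 participants, 82 postal codes, 2,000 runs per setting, ρ from 0 to 0.5) gave 4.9% to 10.4% at 0.6 admissions per person (Poisson) and 4.8% to 14.8% at 0.8 (k = 1). Values of 20% to 26% appeared only at 1.5 admissions per person, overdispersed, with ρ of 0.3 to 0.5.

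**Step 4. The alternative measure.** In the same simulations, a Welch test on total days per randomised participant, zeros kept, rejected in 4.1% to 5.6% of runs. With a postal-code intraclass correlation of 0.05 (0.8 admissions per person, k = 1, ρ = 0.3) it rejected in 5.4%.

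**The case against.** The strongest reply is that the Table 2 entry sits in a column on measurement and says what is recorded, not how it is analysed. Days per admission are the raw data from which days per participant would be summed. Section 5 commits to all randomised subjects, section 5.1 speaks of patient and cluster levels only, and the handling of repeat stays is commonly left to an analysis plan that is not shown here.

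Much of this stands, and it rules out several stronger readings that a reader might infer:

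- **That admissions are treated as independent, with a false-positive rate well above 5%.** The text names no such test. The inflation ranges from none to large, depending on admission counts and correlations that the article does not give. The one-fifth with two or more readmissions in the Background concerns pressure-injury readmissions in a local hospital cohort, not all unplanned admissions in this trial.
- **That the summed admission count lacks a denominator.** The same row gives frequency per participant first.
- **That the fault carries into the economic evaluation.** Section 6.2 builds costs from participants' resource use times unit cost, not from mean stay per admission.
- **That a benefit would be reported as harm.** The admission rows beside it keep the never-admitted and would show the drop in admissions.

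The reply does not remove the core point. Table 2 states units for its outcomes, and several neighbouring rows name the participant where this one names the admission. An outcome definition is something the protocol fixes, and as fixed it gives the never-admitted no value.

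**Conclusion.** The point holds as a flaw in an outcome definition. Length of stay per admission compares arms only among participants with a post-randomisation event, which does not fit the intention-to-treat statement, and it can rise while total hospital days fall. The first part follows from the definition itself. The sizes are illustrative: a 15% fall in days beside a 24% rise in mean stay in one constructed example, and 40% to 56% of participants without a value under assumed admission rates. No statement about type I error can be made from the documents.

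Severity is low. Table 2 lists the outcome under Others, participant-level admission outcomes stand beside it, and the sample size in section 2.4 does not rest on it.

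**What to change.** Redefine the outcome in Table 2 as total unplanned hospital days per randomised participant over 1 year, with zero for those not admitted. Compare arms with the participant as the unit, the postal-code cluster in the model and time at risk accounted for, since section 2.4 expects 20% mortality. A negative binomial model with a postal-code random effect and an offset for days at risk would do, as would a difference in means with a cluster bootstrap. Keep days per admission as a descriptive summary.

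Reconcile two inconsistencies in the same edit:

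- **Status:** secondary in section 3.2, Others in Table 2.
- **Timing:** 1 year if available in Table 2, every follow-up visit in Table 3.

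The cost is wording only, because the data are the same. The downside is a skewed outcome with many zeros, and a wider interval than a per-admission comparison would show.
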